### 2.4 Procedure and outcome measures

All eligible older people will receive information about the study and sign an informed consent form prior to participation. Baseline assessment (in person) will include age, sex, history of falls, duration of symptoms, prognosis rating (STarT Back Screening Tool) [33], functional capacity (Short Physical Performance Battery) [34], cognitive function (Mini Mental State Examination), and the primary and secondary outcomes. Primary and secondary outcomes will be assessed (in person) again at the end of the intervention (i.e., 8 weeks after randomization) and at the 6 and 12-months follow-up. Fig 2 represents the flow of participants during the study.

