### 2.5 Randomisation

The randomisation sequence to our two groups of interest (i.e., group-based exercise or control) will be computer-generated by one of the investigators who will not be involved in the recruitment of participants. The sequence will be blocked (block sizes of 4, 6, and 8, in random order). Allocation will be concealed in sequentially numbered, sealed, opaque envelopes. Participants will be stratified by gender (female or male).

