### 2.8 Data analysis

#### Sample size calculation

The sample size calculation was performed using the G*Power 3.1 software. The difference between means of a meta-analysis 1.7 [26] was divided by the standard deviation of the study of Zadro (2019) [55] 4.80 to obtain Cohen’s d. Considering the Cohen’s d, a sample size of 120 participants was calculated (60 in each group), with a statistical power of 80%, alpha of 5%, and 20% dropout rate.

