#### Analysis of treatment effects

The statistical analysis will be performed following the intention-to-treat analysis principles [56, 57]. The blinded statistician will be given coded data, the normality will be tested using the Kolmogorov-Smirnov test and the homoscedasticity of the data will be tested using the Levene test. Then, considering normal distribution, an analysis of mixed linear models (random intercepts and fixed coefficients) will be conducted, which incorporated terms for treatment, time, and the treatment-time interactions. As two physical therapists will be responsible for implementing the GBE will be applied multilevel analyses with participants nested by physiotherapist. In this sense, level 1 being the different time points, level 2 the subject, and level 3 the physical therapists.

Mean differences and their confidence intervals (CIs) at 95% will be presented. Primary outcome results will be interpreted based on the minimal clinically important difference (MCID) estimated for the adult population (i.e., RMDQ > 5 and NRS > 2) points [58]. All statistical analyses will be performed with SPSS (IBM Corp. Released 2013. IBM SPSS Statistics for Windows, Version 22.0. Armonk, NY: IBM Corp).

In addition, the sample will be dichotomized for improvement / maintenance according to the clinically important differences. The absolute risk reduction will be obtained by subtracting the GBE group risk by the control group risk. This data will be used to calculate the number needed to treat (NNT) (100% / by reducing the absolute risk).

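### The primary model's named terms include neither the baseline value of the outcome nor the stratification factor, so efficiency is lost whichever contrast is reported

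*Protocol article*

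**What the plan says.** Section 2.8 of the protocol article (Analysis of treatment effects) specifies a linear mixed model with random intercepts and fixed coefficients, "which incorporated terms for treatment, time, and the treatment-time interactions". The same paragraph adds a hierarchy: "level 1 being the different time points, level 2 the subject, and level 3 the physical therapists". It then promises mean differences with 95% confidence intervals. No covariate is named. The time points are not listed, and the contrast that yields the mean difference is not identified.

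Section 2.5 states: "Participants will be stratified by gender (female or male". Section 2.4 lists, among the baseline assessments, "cognitive function (Mini Mental State Examination), and the primary and secondary outcomes". The outcomes are measured again at 8 weeks, 6 months and 12 months.

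The sample size paragraph in section 2.8 supplies the only figures on effect size. They are a difference ("The difference between means of a meta-analysis 1.7"), a standard deviation ("4.80 to obtain Cohen’s d"), and the result: "a sample size of 120 participants was calculated (60 in each group"), "with a statistical power of 80%, alpha of 5%, and 20% dropout rate".

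**The concern.** Two pieces of information are available before treatment starts and neither is a named model term: the participant's own baseline score, and the factor used to stratify randomisation.

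The baseline score matters more. The stated terms can yield two kinds of treatment contrast. If baseline is a level of time, the treatment-by-time term is the difference between arms in change from baseline. If baseline is not a level of time, or if the group difference at a visit is reported, the estimate makes no use of baseline and carries any chance imbalance in it. In large samples, adjusting for baseline is at least as precise as either.

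This matters here because the planned sample is small for the effect it is meant to detect. Leaving the contrast open also allows it to be chosen after the data are seen.

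**Working it through.** **Inputs from the article.** Difference 1.7, SD 4.80, 60 per arm, 20% dropout, 5% alpha, 80% power. Completers: 60 × 0.8 = 48 per arm. Effect size: d = 1.7/4.80 = 0.354.

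**Assumptions.** The correlation r between baseline and follow-up is not given, so 0.3, 0.5 and 0.7 are used. The SD of 4.80 is taken as a between-person SD, equal at baseline and follow-up. Tests are two-sided, data are complete, and the therapist level is ignored.

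**The plan's own figure.** The two-sample normal formula gives n = 2(1.960 + 0.842)² × (4.80/1.7)² = 126 per arm (127 with the t distribution). With 127 per arm, the total is 254, or 318 after dividing each arm by 0.8 and rounding up. The stated 120 is not reproduced. A one-sided test needs 100 per arm, which is 250 in total after dropout. On the stated inputs, two-sided power with 48 per arm is about 41%.

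**Variance of each contrast, relative to the raw visit difference.**
- Raw visit difference: 1
- Difference in change: 2(1 − r)
- Baseline-adjusted: 1 − r²

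So adjusted/change = (1 − r²)/[2(1 − r)] = (1 + r)/2, and adjusted/raw = 1 − r².

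**Standard errors and power.** The raw SE is 4.80 × √(2/48) = 0.980. The others are 0.980 times the square root of the factor above. Power is Φ(1.7/SE − 1.960).

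| r | Raw: SE, power | Change: SE, power | Adjusted: SE, power | Adjusted/change variance | Adjusted/raw variance |
|---|---|---|---|---|---|
| 0.3 | 0.980, 41% | 1.159, 31% | 0.935, 44% | 0.65 | 0.91 |
| 0.5 | 0.980, 41% | 0.980, 41% | 0.849, 52% | 0.75 | 0.75 |
| 0.7 | 0.980, 41% | 0.759, 61% | 0.700, 68% | 0.85 | 0.51 |

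The t distribution gives values about one point lower or the same: 31%, 40% and 60% for change, and 44%, 51% and 67% adjusted.

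Generalised least squares standard errors for the stated model with four time points, under the constant correlation that a random intercept implies, equal the raw and change columns. A model with a common baseline mean in both arms gives the adjusted column.

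**Reading the table.** Adjustment gains about 13, 11 and 7 power points over the change contrast, and about 3, 11 and 27 over the raw difference. Below r = 0.5 the change contrast is less precise than ignoring baseline; above 0.5 the order reverses.

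**Does adjustment restore 80% power?** With adjustment, the total N for 80% power after 20% dropout is 286, 236 and 160 at the three correlations. The planned 120 suffices only if r is at least √(1 − 48/126) = 0.79.

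**Sex.** If sex explains an assumed 1% to 5% of the variance, power for the visit difference rises from 41.1% to between 41.4% and 42.9%. A constant sex effect cancels within each person from the change contrast. With SD set to 1, that standard error is 0.2415, 0.2041 or 0.1581 at the three correlations, with or without sex.

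**The case against.** The strongest reply is that this is a condensed journal article. It says that the model incorporated three terms, not that it contained only those; the therapist level appears just afterwards. A covariate list may sit in a plan that is not shown. That is a fair caution: the article does not say the analysis is unadjusted. But it does name the primary model's terms, and no reading of the named terms produces an estimate adjusted for baseline or stratum. The point is an improvement to a stated model rather than a complaint about missing detail.

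Several stronger readings are tempting and should be resisted.

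- A reader might infer that baseline enters only as another repeated measure. This is plausible given the assessment schedule, but section 2.8 never says so. If it does, the change contrast makes real use of baseline: at r = 0.7 its power is 61%, against 41% for the raw difference. Precision is then partly kept, and chance baseline imbalance is removed by subtraction.
- A reader might infer that omitting sex makes the standard errors materially too large. A constant sex effect drops out of the change contrast, and the effect on a visit difference is slight over the assumed range.
- A reader might read the power figures as applying to both primary outcomes. The sample size paragraph does not say which outcome the 1.7 and 4.80 refer to, or what kind of SD 4.80 is. The variance ratios do not need those figures; the power percentages do.

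**Conclusion.** The point holds as one of efficiency. The named terms leave out the baseline value and the stratification factor, and the role of baseline and the reported contrast are not fixed. Relative to adjustment, variance is inflated whichever contrast is meant. The adjusted variance is 15% to 35% lower than that of the change contrast and 9% to 49% lower than that of the raw visit difference, over assumed correlations of 0.3 to 0.7. The size depends on a correlation that the article does not give and on the equal-variance assumption. The power figures also depend on treating 1.7/4.80 as a between-person effect size.

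The documents do not support a claim of bias: under randomisation both contrasts are unbiased. Nor do they support the idea that adjustment rescues the trial's power. At the assumed correlations it leaves power at 44% to 68%, so the sample size calculation remains a separate and larger problem. The reason to include sex is consistency between analysis and stratified randomisation, not a meaningful gain in precision.

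**What to change.** In section 2.8, define the outcomes of the primary model as the three follow-up values (8 weeks, 6 months, 12 months). Name the fixed effects as treatment, time, treatment-by-time, the baseline value of that outcome, baseline-by-time, and sex. A longitudinal model that includes baseline as an outcome with a common mean in both arms, plus sex, is an acceptable alternative. State that the reported estimate is the adjusted mean difference between arms at each follow-up.

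The cost is a sentence or two in section 2.8. All the variables are already collected, and neither sample size nor schedule changes. The change should be recorded before allocation is revealed to the statistician.

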### 2.6 Blinding

The statistician will be blinded to treatment allocation. The data will be coded in an unidentifiable manner and will not contain any information that can reveal what group a single participant or a group were randomised to. As this is an exercise program, it will not be possible to blind the therapist and the patient. Also, because our outcomes are Patient‐Reported Outcome Measures (PROMs), it will not be possible to blind the assessor. However, PROMs are validated and widely accepted in research and the clinic.

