### 2.7 Intervention

#### Group-based exercise

The group-based exercise (GBE) programme will be delivered by two physical therapists (experience in musculoskeletal rehabilitation in primary health care). The GBE comprises three sessions per week of group-based exercise in a local community center, for 8 weeks [44]. Each group session will consist of 10 to 18 participants and each exercise session will last 60 minutes and consist of four stages: (1) five minutes warm up (i.e., self-regulated walk); (2) twenty minutes of moderate intensity walking; (3) thirty minutes of resistance training for the major muscles of the leg, trunk and arm and balance exercises that progress in difficulty; and (4) five-minute cool down period (i.e., self-regulated walk). The exercise intensity will be assessed by one of the following criteria: (1) point of volitional fatigue [45] for the resistance training component; and (2) perceived effort ranging from 3 to 4 on the modified 10-point Borg scale score for the walking component [45]. The intensity will be increased along the 8-week programme following the recommendations of the ACSM guideline [32] (i.e., resistance exercise- a gradual progression of more repetitions per set; and aerobic exercise- a gradual progression of exercise volume by adjusting exercise intensity) [32].

The GBE programme was set up based on tasks that makes part of performance-based assessment instruments widely used for the evaluation of physical performance of the older people (i.e., Berg Balance Scale [46], Dynamic Gait Index [47] and Timed Up and Go [48]). In addition, exercises commonly used in primary health care groups were added [49–51]. The protocol will take place in a gymnasium and will be supervised by a trained physical therapist [52–54]. Examples of the choices of exercises are provided in the S1 Appendix.

Modifications were performed after registration of the clinical trial. We included 5 minutes of warm-up and 5 minutes of cool-down during the intervention. To reduce the risk of injury during the protocol. Furthermore, based on recommendations of the ACSM guideline, criteria were established to intensity increase along the 8-week. All these changes were made before starting to recruit participants. Furthermore, the registry has been updated and is available with new information.

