#### Control group

Participants randomly allocated to control group will remain on a waiting list. In addition, weekly contact will be made to ensure that they do not start treatment during the study protocol. However, previous treatments like medications will be allowed.

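### The primary model nests every participant in one of two therapists, but waiting-list controls have no therapist, and clustering from the exercise sessions is not modelled

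*Protocol article*

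**What the plan says.** Section 2.8 (Analysis of treatment effects) states the model for the trial outcomes: "an analysis of mixed linear models (random intercepts and fixed coefficients) will be conducted", with terms for treatment, time and their interaction. It then adds a cluster level, for the reason given here: "As two physical therapists will be responsible for implementing the GBE". The result is "multilevel analyses with participants nested by physiotherapist", with "level 1 being the different time points, level 2 the subject, and level 3 the physical therapists". No exception is made for the control arm, and the exercise group is not a level.

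Three other sections bear on this:
- Section 2.7, Control group: "Participants randomly allocated to control group will remain on a waiting list". These participants receive a weekly contact and no therapist-led treatment.
- Section 2.7, Group-based exercise: "Each group session will consist of 10 to 18 participants".
- Section 2.6: the coded data given to the statistician "will not contain any information that can reveal what group a single participant or a group were randomised to".

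Section 2.4 has the primary outcomes measured at baseline, 8 weeks, 6 months and 12 months. Section 2.8 promises mean differences with 95% confidence intervals. It does not say whether these are between-arm differences at a follow-up or treatment-by-time contrasts against baseline.

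**The concern.** The authors rightly see that therapist-delivered treatment can make outcomes correlated, but the level they chose does not match the design in three ways.

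1. Half the sample has no unit at level 3, so someone must invent a code for the controls before the model can be fitted.
2. Level 3 has two units, which is too few for a usable variance estimate.
3. People in the exercise arm train together, and that source of correlation is left out.

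Both primary outcomes rest on this model. At stake are the width of their confidence intervals and the true error rate of their tests. There is also a tension with blinding, because a therapist code filled in only for the exercise arm would tell the statistician who was in that arm.

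**Working it through.** **Inputs from the protocol article.** 60 per arm and 20% dropout, so 48 per arm analysed (section 2.8); two therapists, exercise arm only (2.8); sessions of 10 to 18 (2.7); four time points including baseline (2.4). Sixty people in groups of 10 to 18 would make 60/18 = 3.3 to 60/10 = 6 groups if membership is fixed, which the article does not state.

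**Assumptions.** The article gives no ICC, so 0 to 0.10 is used. It has no figure of its own on clustering to reproduce. Standard errors (SEs) below are in units where participant and residual variances are 0.5 each, so they sum to 1 at any one visit.

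**Step 1: how often the therapist variance is estimated as zero.** With two therapists of 24 analysed participants each, the probability is P(F(1,46) < 1/(1 + 24·ICC/(1−ICC))).

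| ICC | 0 | 0.01 | 0.02 | 0.05 |
|---|---|---|---|---|
| P(estimate = 0) | 0.68 | 0.63 | 0.58 | 0.49 |

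**Step 2: between-arm difference at one follow-up.** With 60 per arm the SE without clustering is √(2/60) = 0.183. Take a therapist variance of 0.05, with 30 participants per therapist:

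| Coding of controls | Added variance | SE |
|---|---|---|
| Split between the two therapists | 0 (cancels) | 0.183 |
| No therapist effect | 0.05/2 = 0.025 | 0.242 |
| A third unit of their own | 0.05/2 + 0.05 = 0.075 | 0.329 |
| For comparison: same variance in four exercise groups of 15 | 0.05/4 = 0.0125 | 0.214 |

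None of the three codings gives the SE that applies when the clustering lies in exercise groups.

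**Step 3: treatment-by-time contrast with baseline as a time point.** A therapist intercept is constant over time, so it drops out of any change from baseline. Generalised least squares with four visits and complete data gives an SE of 0.1826 for this contrast under all three codings and therapist variances of 0, 0.05 and 0.10. The coding no longer matters, but the level also does nothing: correlation that develops during the 8 weeks of training is not captured.

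**Step 4: group clustering not captured.** With clustering in one arm only, the design effect is DE = 1 + (m−1)·ICC, the variance factor is (1 + DE)/2, and the type I error is 2·(1 − Φ(1.96/√factor)). Example for m = 14 and ICC 0.05: DE = 1.65, factor = 1.325, SE ratio = 1.151, error = 0.089.

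| ICC | SE ratio, m = 10 to 18 | True two-sided type I error |
|---|---|---|
| 0.01 | 1.02 to 1.04 | 5.5% to 6.0% |
| 0.02 | 1.04 to 1.08 | 6.0% to 7.0% |
| 0.05 | 1.11 to 1.19 | 7.7% to 10.1% |
| 0.10 | 1.20 to 1.36 | 10.4% to 15.0% |

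**Step 5: simulation with estimated variances.** 4,000 null trials per setting, four groups of 15 under two therapists, one follow-up, z-test. Type I error:

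| Model | Group ICC 0.05 | Group ICC 0.10 |
|---|---|---|
| No cluster term | 9.4% | 14.4% |
| Therapist level, controls split | 9.6% | 14.6% |
| Therapist level, controls as third unit | 6.0% | 8.4% |
| Therapist level, controls without effect | 6.9% | 9.9% |
| Group effect, exercise arm only | 6.5% | 8.5% |

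The third-unit coding is not a safe choice either. With no clustering at all, its mean SE was 0.223 against a true 0.184.

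**The case against.** The strongest reply is that the natural reading of the model makes the effect a treatment-by-time contrast, from which the therapist intercept cancels. Step 3 confirms this. A reader might infer that the primary confidence interval always depends on how controls are coded, or that the test falls to 1 degree of freedom with a critical t of 12.7. The documents do not support that in general. It can arise only for a between-arm difference at a follow-up, and the 1-df case only if controls form a third unit. The same argument applies to the remedy: an exercise-group effect that is only an intercept would also cancel, so it must be able to act after baseline.

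A second reply is that, at a single follow-up, two of the three codings perform about as well as the group model under a z-test (6.0% and 6.9% against 6.5% at ICC 0.05). That stands. No gain in type I error over those two codings has been shown. The case for the group model is that it puts the clustering where it can arise and gives every control a defined unit.

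A third reply is that the ICC is assumed and that the article gives a session size, not fixed cohorts. Both are true. At ICC 0.01 to 0.02 the inflation is modest, and a firm count of groups would be an inference.

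A fourth reply is that coding details belong in an analysis plan that is not shown. That holds for the coding and for the degrees-of-freedom method. It does not hold for the hierarchy, which the article states in full and which does not match its own control arm.

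**Conclusion.** Wrong as written. The stated third level does not fit a waiting-list arm, rests on two units, and leaves out clustering from group sessions. That much follows from the article without any assumed figure.

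The size and direction of the error are uncertain:
- For a between-arm difference at a follow-up, the SE runs from 0.183 to 0.329 by coding alone, against 0.214 under four groups of 15, all at an assumed variance of 0.05.
- For the treatment-by-time contrast, the therapist level has no effect, and any post-baseline group clustering goes uncaptured.
- Uncaptured clustering gives a type I error between about 5.5% (ICC 0.01) and 15% (ICC 0.10, groups of 18).

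Three stronger readings are not supported. A reader might infer that the therapist variance cannot be estimated; it can, but very poorly, with a non-zero estimate in 32% to 51% of trials. A reader might infer that the SE is certain to be seriously wrong; with a small ICC the error may be slight. A reader might infer that the statistician's blinding is already broken; that depends on a coding the article does not show. Even so, a therapist code filled in only for the exercise arm would conflict with section 2.6, so the two sections need reconciling.

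**What to change.** - **Model.** Replace level 3 with a partially nested model: a random exercise-group effect in the exercise arm only, each control as its own unit, and Satterthwaite degrees of freedom. The group effect must apply to post-baseline visits, either as a group-by-time term or by modelling follow-up outcomes with baseline as a covariate.
- **Effect reported.** State whether the reported mean difference is a between-arm difference at each follow-up or a contrast against baseline.
- **Therapist.** Use therapist as a fixed factor in a sensitivity analysis within the exercise arm. If both therapists lead every session together, which the article does not rule out, a therapist effect cannot be identified and this analysis should be dropped.
- **Data.** Record each participant's exercise group during delivery, since it may not be recoverable later.
- **Blinding.** Fix the model code on dummy labels before group or therapist codes are released, and amend section 2.6 to say so.

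The cost is a change of wording and one extra data field. The downside is somewhat wider confidence intervals and few degrees of freedom for the group effect. Some anti-conservatism may remain, because there would be only about 3 to 6 groups if membership is fixed (6.5% at ICC 0.05 in the z-test simulation).

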**Discussion:**

Our hypothesis is that group-based exercise will be better than waiting list in reducing pain intensity and disability in older people with chronic non-specific low back pain.

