## 1. Background

Low-back pain (LBP) is one of the most common health conditions worldwide [1]. It is defined as pain below the costal margin and above the inferior gluteal folds, with or without referred leg pain [2, 3]. It is expected that 70% to 85% of the general population will present an episode of LBP during lifetime, including older people (i.e., 60 years old or over) [4, 5]. The most common form of LBP is non-specific [6], defined as the symptoms without a specific cause [7, 8]. Older people with chronic non-specific (CNS) LBP reports disability [9, 10], productivity loss [11] and low quality of life (QOL) [12].

Current guidelines recommend management of chronic health conditions in older people at primary health care settings using active strategies (e.g., exercise) to decrease pain intensity, disability, productivity loss and health care costs [3, 13, 14]. In primary health care, group-based exercise is often used to manage older people [15, 16] because it has shown to be cost-effective for older people with different health conditions [17–19]. For instance, this active strategy is effective for prevention and fear of falling [17, 18], improvement of QOL [17] and balance [17, 20] in the older population.

In CNSLBP, high quality evidence supports active strategies such as exercise for general population [3, 14, 21–25]. Previous systematic reviews also showed promising efficacy of exercise on pain intensity and disability related to CNSLBP in older people [26]. However, the management of CNSLBP in this population has been overlooked and evidence is limited to a small number of low powered randomized controlled trials with high risk of bias [27, 28]. Moreover, efficacy of group-based exercise has not been investigated in older people with CNSLBP [26, 28]. Thus, the primary aim of this randomized controlled trials is to investigate the efficacy of an 8-week group-based exercise program on pain intensity and disability in older people with CNSLBP in a primary health care setting. Our secondary aims are to investigate efficacy on global impression of recovery, frequency of falls, fear of falling and physical activity (PA) level.

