#### Primary outcomes

Pain intensity over the previous week (measured with a 0–10 points in numeric rating scale [NRS]): The NRS is a self-reported scale in which the patient can select one number that best describes the pain intensity. The score ranges from 0 to 10; higher scores represent higher levels pain intensity. This scale was previously validated for population with low back pain [35, 36].Disability (measured with the 0–24 points in Roland-Morris Disability Questionnaire [RMDQ]): The RMDQ is a self-reported scale of 24 items in which the patient reports pain-related disability. The score per item ranges from 1 (yes) to 0 (no). Total score ranges from 0 to 24, higher scores represent higher levels of pain-related disability. This instrument was previously validated for the low back pain Brazilian population [37, 38].

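### Pain and disability are both primary at three visits, but no primary time point and no rule for claiming success is fixed, so the type I error is not fixed at 5%

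*Protocol article*

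**What the plan says.** - **Outcomes.** Section 2.4 (Primary outcomes) lists two: "Pain intensity over the previous week" on the 0–10 NRS, and disability on the 0–24 RMDQ. The primary aim in section 1 names both: "efficacy of an 8-week group-based exercise program on pain intensity and disability in older people with CNSLBP".
- **Visits.** Section 2.4 schedules the primary outcomes "at the end of the intervention (i.e., 8 weeks after randomization) and at the 6 and 12-months follow-up". None of the three is called primary, there or elsewhere.
- **Model and reporting.** Section 2.8 (Analysis of treatment effects) plans a mixed model "which incorporated terms for treatment, time, and the treatment-time interactions", so there is one treatment contrast per outcome per visit. It adds: "Mean differences and their confidence intervals (CIs) at 95% will be presented". Primary results are to be read against an MCID (RMDQ > 5, NRS > 2), with no visit attached.
- **Sample size.** Section 2.8 uses one mean difference (1.7) and one SD (4.80), "with a statistical power of 80%, alpha of 5%, and 20% dropout rate". The paragraph names neither an outcome nor a visit.
- **Hypothesis.** The abstract expects that "group-based exercise will be better than waiting list in reducing pain intensity and disability in older people". It does not say at which visit, or whether one positive outcome would be enough.
- **Singular or plural.** Section 3.2 says the trial is powered for the primary outcome, in the singular, although section 2.4 lists two.

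**The concern.** A 95% interval that excludes zero is equivalent to a two-sided 5% test. Two outcomes at three visits give six such intervals, all belonging to primary outcomes. The plan does not say which of them the hypothesis stands or falls on, so the same data could support a positive or a negative conclusion depending on a choice made after the results are known.

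Three features make this matter more here. The trial is unblinded, has a waiting-list control and uses patient-reported outcomes, so pre-specification is one of its few protections against selective claims. The visits also answer different questions: 8 weeks addresses the effect of the programme at its end, and 6 and 12 months address whether it lasts. Finally, the planned improved/not-improved split and the number needed to treat inherit the same gap, since they too could be computed at any of three visits.

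**Working it through.** **1. The plan's own figure.** The only design figure stated is the sample size. d = 1.7/4.80 = 0.354. Per group, n = 2(1.960 + 0.842)²/0.354² ≈ 125.1, so 126 (two-sided 5%, 80% power). That is 252 in total, or 252/0.8 = 315 with 20% dropout. One-sided, it is 99 per group, or 198/0.8 = 248 in total. The stated 120 does not reproduce under either. That is a separate matter. What counts here is that the calculation covers one comparison with an undivided 5%.

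**2. Six independent tests.** 1 − 0.95⁶ = 26.5%.

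**3. Six correlated tests.** The contrasts share patients, so independence overstates the error. Simulation: 1,000,000 draws of six normal z-statistics with no true effect; correlation r_v between visits, r_o between outcomes, and r_v × r_o across both; threshold |z| > 1.96. The correlations are assumptions.

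| r_v / r_o | Any of six, either direction | Any of six, favouring exercise | One outcome, any visit | Both outcomes, each at any visit |
|---|---|---|---|---|
| 0.3 / 0.3 | 24.8% | 12.6% | 13.6% | 2.4% |
| 0.5 / 0.5 | 22.0% | 11.1% | 12.6% | 3.2% |
| 0.7 / 0.7 | 17.7% | 8.9% | 11.0% | 4.2% |

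With unequal correlations in the same range, the last column runs from 1.7% (0.7 / 0.3) to 5.3% (0.3 / 0.7). At 0.8 / 0.8 the first column falls to 14.9%. The reference value for the column favouring exercise is 2.5%, one tail of a single two-sided 5% test.

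The last column assumes no effect on either outcome. If exercise truly and strongly improved one outcome and not the other, a false claim for both would need only the null outcome to reach significance at some visit. The error then approaches the one-outcome column, about 11–14%. A both-must-succeed rule holds 5% in that case only if the visit is fixed.

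**4. After naming one visit.** Two outcomes at 5% each, either sufficing: 1 − 0.95² = 9.75% if independent, and 8.3–9.5% at correlations of 0.7 to 0.3. At 2.5% each: 4.3–4.9%. Holm keeps the overall error at or below 5%. Requiring both at 5% needs no alpha split.

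**5. Cost in power.** Completers per group: 60 × 0.8 = 48. The normal approximation to the detectable difference at 80% power is (z for alpha + 0.842) × √(2/48): 2.802 × 0.204 = 0.57 at 5%, and (2.241 + 0.842) × 0.204 = 0.63 at 2.5%. The noncentral t gives 0.578 and 0.638.

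**The case against.** **The plan never says that six tests are run at 5%, or that any one of them is success.** This is right, and it limits the point. A reader might infer that the trial has a false-positive rate of 18–25%. The documents do not support that as a fact. It needs an either-outcome, any-visit rule that the protocol does not state, it rests on assumed correlations, and it counts errors in both directions although the hypothesis is directional. The hypothesis joins pain and disability with an and, and read strictly that gives a far lower figure. What stands is that no rule is written, so neither the high nor the low figure can be ruled out.

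**Primary results will be interpreted against the MCID.** With the protocol's SD and 48 per group, the standard error of an RMDQ difference is 4.80 × √(2/48) = 0.98, so 5 points is about 5.1 standard errors. A chance difference that large would be very rare. For the NRS the protocol gives no SD; assuming 2 to 3 points, the standard error is about 0.41–0.61, and 2 points is about 3.3–4.9 standard errors. A false claim of a clinically important effect is therefore unlikely. But the protocol uses the MCID as a guide to interpretation, not as a condition for success, so it does not control the error of a claim that exercise is better than waiting list.

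**Multiplicity procedures belong in an analysis plan, and this is a condensed article.** This is fair for the choice of procedure. It does not reach the primary time point, which is part of the definition of a primary outcome and of the basis for the sample size. Nor does it explain why the article lists two primary outcomes in one section and speaks of one in another.

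**Eight weeks in the aim describes the length of the programme, not an endpoint.** This is also fair. It makes 8 weeks the natural choice, not the only one.

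**Conclusion.** The point holds as a gap in specification. Two primary outcomes, three visits, unadjusted 95% intervals, no primary time point and no rule for a claim sit beside a sample size for one comparison at 5%. The type I error is therefore undetermined. Under assumed correlations of 0.3–0.7 it runs from about 2% (both outcomes required, each at any visit, no effect on either) to about 25% (any one contrast suffices). The visit question alone takes a single outcome from 5% to about 11–14%, so it would remain even with one primary outcome. The facts about the plan are certain. The percentages are conditional on the claim rule and on the correlations, and should be quoted only with those conditions. This is a cheap improvement that should be made.

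**What to change.** 1. Before the statistician is unblinded or any results by arm are seen, name one primary time point. The treatment difference at 8 weeks, the end of the programme, fits the stated aim. Make the other visits secondary.
2. State the rule for the two outcomes: either both must be significant at 5%, or either suffices with Holm at an overall 5%. The choice is the investigators'.
3. Say that the MCID reading, the improved/not-improved split and the number needed to treat refer primarily to that visit.
4. Align the sample-size paragraph, the singular wording in section 3.2 and the registry entry with these choices.

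**Cost.** A few sentences and a registry update, plus some power. With Holm or an equal split, the detectable d at 48 per group moves from 0.58 to at most 0.64. At the plan's own d of 0.354, power for one outcome at 48 per group is about 40% at 5% and about 30% at 2.5%. Holm loses less than the split, because once one outcome is significant at 2.5% the other is tested at 5%. Requiring both outcomes leaves alpha whole, but joint power falls: with 80% for each, it lies between 0.8 × 0.8 = 64% (independent) and 80% (fully correlated).
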